##### Adherence to and Compliance with the Protocol

To promote adherence to the protocol and facilitate compliance, the following measures will be implemented:Each participant will attend individually, with a pre-established, adapted timetable.The sessions will be supervised and led by a qualified personal trainer and the principal investigator, who will provide ongoing support and motivation.If a participant misses two or more consecutive excused sessions, the intervention period may be extended by up to four additional weeks to allow time for recovery.

To comply with the protocol, participants must:Complete at least 90% of the scheduled sessions.Carry out all scheduled assessments within 20 weeks.Do not make significant changes in their daily lives that could interfere with the results or safety of the study. Specifically, participants will be instructed:○To maintain their usual dietary habits and not to start any special diets or significant nutritional supplementation without consulting the research team.○To refrain from starting new intense physical exercise programmes or substantially increasing their usual physical activity beyond the IST programme.○Continue with their usual medical care and prescribed treatments, as long as they do not directly interfere with the objectives and safety of the IST (as assessed by the research team). Any relevant new medication or treatment initiated will be recorded (see Section 2.1.3).

Non-compliance with these criteria will be recorded. The criteria for discontinuation or withdrawal from the study are detailed below:

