#### 2.1.5. Assignment of Intervention and Blinding

Assignment of Intervention: This study employs a single-arm design where all participants receive the IST intervention. Therefore, no randomisation procedures, allocation concealment or implementation mechanisms will be applied to assign participants to different groups, as there is only one intervention group to which all eligible consenting participants will be assigned.Blinding:○Participants and Intervention Staff: Given the design and nature of the intervention (physical exercise), neither the participants nor the staff administering the IST (qualified trainer, principal investigator) will be blinded.○Outcome Evaluators and Data Analysts: Measures will be implemented to minimise evaluator bias (detailed in Section 2.1.3). Although complete blinding of lead assessors at the time point (pre/post) is difficult, attempts will be made to ensure that they do not access previous results when making subsequent measurements. For the analysis of static posture photographs, blinding of the analyst at the time of assessment will be attempted. Where possible, the primary statistical analysis shall be performed by a team member not involved in direct data collection; otherwise, the team will seek to analyse the primary data without knowledge of the temporal coding until preliminary analyses are completed, if feasible.Unblinding Procedure: Since there is no blinding of participants or staff to different treatment arms and the intervention is known, formal unblinding procedures are not applicable. In case of a serious adverse event, its relationship to the known IST intervention will be assessed according to safety protocols.

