1.Other Indicators of Sarcopenia and Dynapenia:○Handgrip Strength: Specific measurement variable: Maximal handgrip strength, measured in kilograms (kg) (Jamar Dynamometer). Analysis metric: Absolute change from baseline to week 17. Method of aggregation: Mean and SD. Time point(s): Baseline (week 0) and post-intervention (week 17). Clinical Relevance: A component of the sarcopenia diagnosis and a predictor of functionality and mortality.○Gait Speed: Specific measurement variable: Usual gait speed over a 4 m course, measured in meters/second (m/s) (Newtest Powertimer). Analysis metric: Absolute change from baseline to week 17. Method of aggregation: Mean and SD. Time point(s): Baseline (week 0) and post-intervention (week 17). Clinical Relevance: A measure of physical performance, a component of the sarcopenia diagnosis, and a predictor of adverse outcomes.○MVIC of other muscle groups: Specific measurement variable: MVIC for the peck deck, pull over, lateral shoulder elevation, leg curl, low back, hip abduction and hip adduction, measured in Newtons (N) (CIEX SYSTEM). Analysis metric: Absolute change from baseline to week 17. Method of aggregation: Mean and SD of the change per exercise. Time point(s): Baseline (week 0) and post-intervention (week 17). Clinical Relevance: Assesses the training response across different body regions.○Sarcopenia Status: Specific measurement variable: Diagnostic status of sarcopenia according to EWGSOP2 criteria (based on muscle strength, muscle mass, and physical performance). Analysis metric: Change in the proportion of participants meeting the diagnostic criteria from baseline to week 17. Method of aggregation: Frequencies and percentages. Time point(s): Baseline (week 0) and post-intervention (week 17). Clinical Relevance: Quantifies the overall impact of the intervention on the diagnostic status of the condition.2.Health-Related Quality of Life (HRQoL):○Specific measurement variable: The index score derived from the EQ-5D-5L descriptive system and the Visual Analogue Scale (VAS) score of the same questionnaire. Analysis metric: absolute change from baseline to week 17 for both the index score and the VAS score. Method of aggregation: Mean and SD of the changes. Time point(s): Baseline (week 0) and post-intervention (week 17). Clinical Relevance: Measures the overall self-perceived health and the impact of the intervention on multiple dimensions of participant well-being.3.Applicability of the IST Protocol:○Perceived Safety: Specific measurement variable: Score on a 5-point Likert scale for perceived safety. Analysis metric: Mean score post-intervention. Method of aggregation: Mean and SD. Time point(s): Post-intervention (week 17). Relevance: Assesses the participant’s subjective perception of safety, providing data to test hypothesis H1.○Acceptance/Satisfaction: Specific measurement variable: (1) Adherence rate (% of completed sessions); (2) Score on a 5-point Likert scale for overall satisfaction. Analysis metric: Percentage for adherence; Mean score post-intervention for satisfaction. Method of aggregation: Percentage for adherence; Mean and SD for satisfaction score. Time point(s): Adherence monitored continuously during the intervention (weeks 1–16); Satisfaction assessed post-intervention (week 17). Relevance: Measures the feasibility and appeal of the intervention to participants, providing data to test hypothesis H2.○Perceived Difficulty: Specific measurement variable: Score on a 5-point Likert scale for perceived difficulty. Analysis metric: Mean score post-intervention. Method of aggregation: Mean and SD. Time point(s): Post-intervention (week 17). Relevance: Evaluates the perception of technical simplicity, providing data to test hypothesis H3.○Adverse events: Specific measurement variable: Incidence, type, severity and causality (relationship to IST). Analysis metric: Frequencies and descriptive summary. Method of aggregation: Counts and percentages. Time point(s): Monitored continuously during the intervention period (weeks 1–16). Relevance: Assesses the objective safety profile of the protocol, providing data to test hypothesis H1.

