#### 2.2.2. Pre-Intervention Assessment

One week before starting the 16-week IST, a comprehensive baseline assessment will be performed on the selected subjects to collect baseline data. This assessment, conducted by a physical activity professional and the research group doctor, will allow for detailed monitoring and accurate assessment of the effects of the programme, including the following variables:Physiological Variables: BP and heart rate HR (Omron M3 Comfort^®^ blood pressure monitor, HEM-7134-E, Omron Healthcare Co., Kyoto, Japan) and O2 saturation (OXYM4000 pulse oximeter, Quirumed S.L.U., Valencia, Spain) will be measured. Three resting measurements will be taken per participant, using the mean as the final data.Functional Capacity:○MVIC: The MVIC of each muscle group of the IST programme will be assessed at individualised intermediate angles (determined according to anatomical structure and motor restrictions, recorded with a HALO© digital goniometer). The CIEX SYSTEM machine (Ciex Systems©, Durango, Spain) with sensors and Chronojump software (Chronojump Boscosystems^®^, Barcelona, Spain) will be used for instantaneous measurement and visualisation of strength, tools also used in all IST sessions and for monitoring purposes.○Static Posture Assessment: Participants will be photographed in anatomical position (frontal and sagittal planes) with a Casio Exilim Pro EX-F1 camera (configuration: level tripod, lens at umbilical height, at 4 m, optical zoom, aperture priority, focal length 50 mm, f5.6, ISO 200) [81]. An analysis of documented validity and reliability for postural analysis will be performed with Kinovea^®^ software (v.0.9.x+) [82,83]. Adhesive markers or direct image identification may be used for key anatomical points [84] (sagittal: tragus, C7, acromion, greater trochanter, lateral femoral epicondyle, peroneal malleolus; frontal: acromions, anterior superior iliac spine (ASIS), posterior superior iliac spine (PSIS), patellar centre, tibial malleoli). Postural parameters will be calculated from these points (sagittal: head-neck alignment (HNA) [82], shoulder alignment, estimated spinal curvatures, pelvic tilt [84], knee alignment; frontal: head tilt/symmetry, shoulder height, pelvic symmetry [81], lower limb alignment [82]). Angles (degrees) and distances (cm/mm, after calibration if size reference is used) shall be recorded. Pre-post change will be an outcome of interest. Image analysis shall be performed, if possible, by a blinded assessor (see Section 2.1.3) [83].HRQoL: The EuroQol EQ-5D-5L questionnaire (5 items, 5 dimensions, 5 response levels) will be used [85,86]. This instrument includes two parts: a descriptive system comprising five dimensions (mobility, self-care, usual activities, pain/discomfort, anxiety/depression), each with five response levels, and a VAS where participants rate their overall health.Applicability of the IST Protocol (scales administered post-intervention):○Safety (H1): Assessed by: (1) Analysis of Adverse Events (AEs) (incidence, type, severity, relationship to IST) over 16 weeks (procedures detailed in Section 2.4.3); ‘low risk’ if the incidence of IST injuries is minimal. (2) Perceived Safety: 5-point Likert scale (1 = extremely unsafe, 5 = extremely safe) post-programme, with face validity and based on similar approaches [87]; a mean score ≥ 4 will be expected.○Acceptability (H2): Assessed by compliance rates (≥90% sessions) and overall satisfaction (5-point Likert scale: 1 = extremely dissatisfied, 5 = extremely satisfied) post-programme, using validated measures [88]; a mean satisfaction score ≥ 4 will be expected.○Difficulty (H3): Assessed with a 5-point Likert scale on perceived challenge (1 = not challenging at all, 5 = extremely challenging) post-programme, validated approach [89]; a mean score ≤ 2 will be expected.Genetic Analysis: Saliva samples will be collected using buccal swabs (4N6FLOQSwab, Life Technologies, Waltham, MA, USA). DNA will be extracted from these samples (QIAmp DNA Mini kit, Qiagen, Venlo, The Netherlands) and subsequently quantified (Qubit, Life Technologies). Genetic polymorphisms, specifically Single Nucleotide Polymorphisms (SNPs) and Insertions/Deletions (INDELs), will be analysed in genes associated with the response to strength training, hypertrophy, and strength gains [63,64,65,66,67,68,69,71,72,73]. Specifically, genes linked to the following will be analysed:○Muscle fibre typology: such as ACTN3 (R variant associated with a higher proportion of type II fibres, crucial for strength/power and affected by sarcopenia/dynapenia in ageing) [63,64].○Response to training: including ACE [63,65,66], NRF2, CKMM, MCT1, AMPD1, and the co-activators PPARGC1A and PPARGC1B (involved in mitochondrial biogenesis and exercise adaptation).○Muscle fibre damage and regeneration: genes such as IGF2, MLCK, CASP [72], MMP3 [72], TNC and GDF5 [73], which influence the response to exercise microtrauma and its repair. Moderate exercise-induced muscle damage (EIMD), potentially triggered by IST at long angles, is considered to contribute to remodelling and adaptation.○Vascularisation: NOS3 and VEGFA [67,69], essential for oxygen/nutrient supply, muscle growth and recovery, optimising metabolic stress and hypertrophic response.○Inflammation: TNF-α, CRP [60], IL-6 [60] and IL6-R, which are relevant because inflammation contributes to sarcopenia and modulates the anabolic response [70].○Oxidative damage response capacity: SOD2 [71], CAT and GPX, crucial for muscle recovery and adaptation to training stress.○Fat and carbohydrate metabolism (nutrigenomic factors): Polymorphisms in FABP2, ADRB2, ADRB3, FAT/CD36, UCP2, GCKR, ADCY5 and GIPR, which may influence nutrient uptake and hypertrophic response [74,75,76].

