#### 2.3.2. Analysis Strategy

Primary and secondary quantitative variables will be compared pre-post with Student’s *t*-tests for related samples, after testing for normality (Shapiro-Wilk). If the data are not normally distributed or contain outliers, non-parametric tests (e.g., the Wilcoxon signed-rank test) will be employed. Effect sizes (Cohen’s d) and confidence intervals will be calculated. Multivariate analyses will include a multiple linear regression to explore the influence of genetic and environmental variables on strength and muscle mass improvement, with Bonferroni correction for genetic analyses. Qualitative variables (e.g., sarcopenia diagnosis) will be analysed by using McNemar tests. Applicability variables (Likert scales, adverse events) will be analysed with descriptive statistics and *t*-tests or Wilcoxon tests for pre-post comparisons on Likert scales. Additionally, exploratory subgroup analyses will be performed to assess whether the response to IST on primary variables differs according to sex, age ranges (70–79 vs. ≥80 years) and baseline severity of sarcopenia/dynapenia. Adjustment for baseline covariates will be considered in regression models. The software will be IBM SPSS v29.0 and R v4.3.1.

For the assessment of the secondary hypotheses concerning the applicability (Section 2.2.2) of the IST protocol, specific analyses will be carried out:

Hypothesis H1 (low injury risk): This will be assessed through two approaches. First, Adverse Events (AEs) will be recorded (including their type, severity, and causality), and ‘low risk’ will be inferred if the incidence of IST-related injuries is minimal and comparable to or lower than rates reported in the literature for strength training in older adults [1,33,34,35]. Second, Perceived Safety will be measured post-intervention using a 5-point Likert scale; the approach for this subjective scale is based on similar methods used in previous research [87]. The hypothesis will be supported by a mean score of ≥4.

Hypothesis H2 (high acceptance): This will be assessed by: (1) compliance rate, with a success threshold of ≥90% of completed sessions, and (2) a satisfaction score from a 5-point Likert scale administered post-intervention, using a validated measurement approach [88]. The hypothesis will be supported by a mean satisfaction score of ≥4.

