#### 2.4.3. Collection, Assessment, Reporting and Management of Adverse Events (AEs)

Active safety monitoring will be performed throughout the study.

Collection: In each training session, the trainer will actively ask about unusual complaints or symptoms (requested AEs). Participants will be instructed to spontaneously report any AEs between sessions to the principal investigator or trainer. All AEs will be systematically recorded.Assessment: The description, dates, intensity (mild, moderate, severe), seriousness (if Serious Adverse Event—SAE), measures taken and causality (relationship to SAE) of each AE will be documented by the principal investigator and the study doctor. A SAE will be defined as one that results in death, is life-threatening, requires hospitalisation/prolongation of life, results in significant disability/incapacity, or is a congenital anomaly.Reporting: All AEs will be recorded in each participant’s CRF. AEs will be reported to the Research Ethics Committee of the University of Deusto according to its regulations and deadlines.Management: Care will be provided in the event of an AE. If the AE is mild and related to the intervention, a temporary break may be considered (although progression is standardised). If the AE is moderate, severe, or considered a SAE, or if deemed necessary for participant safety by the principal investigator or study doctor, discontinuation of the participant’s involvement will be considered (as detailed in Section 2.1.2). Any participant who suffers harm as a result of trial participation will receive appropriate medical treatment.

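### H1's injury criterion counts only injuries judged IST-related, and the unblinded principal investigator who delivers the training shares in that judgement

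*Protocol article*

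**What the plan says.** Section 2.3.2 of the protocol article sets the objective part of H1. The low-risk conclusion "will be inferred if the incidence of IST-related injuries is minimal and comparable to or lower than rates reported in the literature"; the literature meant is that on strength training at older ages. Section 2.2.2 gives the same restriction in shorter form, "if the incidence of IST injuries is minimal", without the literature comparison. Neither section puts a number on minimal. Both add a second criterion for H1, a mean perceived-safety score of at least 4 on a five-point scale.

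Section 2.4.3 names who assesses adverse events (AEs). Description, dates, intensity, seriousness, action taken and causality "of each AE will be documented by the principal investigator and the study doctor". It writes the causality item as "causality (relationship to SAE", whereas the outcome list in 2.2.1 has "Incidence, type, severity and causality (relationship to IST".

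On the principal investigator's role, the adherence part of 2.1.2 states "The sessions will be supervised and led by a qualified personal trainer and the principal investigator", and 2.1.5 states that "neither the participants nor the staff administering the IST (qualified trainer, principal investigator) will be blinded". Section 2.4.1 sets up no independent data monitoring committee and makes the principal investigator and the research team, including the thesis supervisors, responsible for safety monitoring. Section 2.4.4 plans no external audit, and 2.1 includes no concurrent comparison group.

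**The concern.** The numerator of a safety criterion passes through a subjective filter, and one of the two people applying it delivers the intervention under test. In people aged 70 and over, a new shoulder, knee or back complaint can sometimes be put down to an existing condition. The exclusion criteria remove severe musculoskeletal disease, but milder pain remains eligible. Each injury attributed elsewhere leaves the H1 count, and every such move favours the hypothesis. No control arm or independent reviewer would show whether the attribution was fair.

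The plan guards against this kind of bias in other places. Sections 2.1.3 and 2.1.5 try to blind the posture analyst to time point, keep earlier results from assessors, and separate the primary analysis from data collection where possible. Nothing comparable protects the causality judgement, although it selects the events that H1 counts. At stake is the credibility of a low-risk statement that the authors intend to carry into a later randomised trial.

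**Working it through.** **1. The passages side by side.**
- Numerator: IST-related injuries only (2.2.2 and 2.3.2).
- Classifier: principal investigator and study doctor together (2.4.3). The section does not say whose view prevails if they differ.
- Deliverers: trainer and principal investigator (2.1.2, 2.1.5). The study doctor is not listed among them.
- Recording: all AEs are recorded (2.4.3) and summarised as counts and percentages with causality as one attribute (2.2.1). The all-injury count can therefore be produced, but the H1 rule does not use it.
- Causality item: relationship to SAE in 2.4.3, relationship to IST in 2.2.1. These are different variables, and only the second can select H1's numerator.

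**2. The denominator.** Section 2.3.1 states 15 evaluable participants (d = 0.80, two-sided α = 0.05, 80% power) and 18 recruited after 15% losses. Exact noncentral-t power for a paired test is 79.0% at n = 14 and 82.1% at n = 15, so 15 is reproduced. 15/(1 − 0.15) = 17.65, rounded up to 18. The point made here does not affect this calculation. The plan states no injury rate, threshold or benchmark value for H1, so there is no H1 figure to reproduce.

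**3. Step size.** One injured participant reclassified: 1/18 = 5.6 percentage points. For example, if three participants are injured and two injuries are attributed elsewhere, the incidence goes from 3/18 = 16.7% (exact 95% CI 3.6% to 41.4%) to 1/18 = 5.6% (0.1% to 27.3%).

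**4. Sensitivity to attribution (assumed inputs).** Let p be the true risk of any injury over the programme and q the share attributed to IST. The documents give neither. The chance that at most one of 18 participants is counted is

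P(≤1) = (1 − pq)^18 + 18·pq·(1 − pq)^17.

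For p = 0.20 and q = 1: 0.0180 + 0.0811 = 0.099. For p = 0.20 and q = 0.5: 0.1501 + 0.3002 = 0.450.

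| Assumed p | q = 1 | q = 0.75 | q = 0.5 | q = 0.25 |
|---|---|---|---|---|
| 10% | 45.0% | 60.4% | 77.4% | 92.7% |
| 20% | 9.9% | 22.4% | 45.0% | 77.4% |
| 30% | 1.4% | 6.3% | 22.4% | 60.4% |

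The cut-off of one injury is chosen only for illustration; the plan sets none. A value of q below 1 is not in itself bias, since some injuries will truly be unrelated to training. The table shows only how strongly the count depends on the attribution step.

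**The case against.** The strongest case on the other side has four parts.

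- **The arrangement is ordinary.** An investigator and a physician documenting causality together is common practice, and the physician here does not appear to deliver the training. This stands in part. A reader might infer that the deliverer alone decides what counts; the text does not support that. It does leave the deliverer with a share of the decision. The absence of a causality scale or adjudication procedure is not held against a journal article.
- **Attribution is visible.** All AEs are recorded, go into the case report form, are reported to the ethics committee, are reviewed in team meetings and are summarised with causality. This stands, and it is why the remedy is cheap. The H1 rule still reads only the related subset.
- **IST-related injury is the quantity H1 is about.** An all-injury count over 16 weeks in this population includes events unconnected with training, and without a control arm that background cannot be subtracted. The cited literature rates may count all injuries or only training-related ones; the documents do not say which. This stands. It is tempting to conclude that the all-injury count should replace the related count, but that would exchange one weakness for another.
- **Nothing flips.** With no number for minimal, no reclassified injury crosses a stated boundary, and H1 also has a participant-rated criterion. This stands as a limit on the size of the point.

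**Conclusion.** The point holds in a limited form. H1's injury criterion depends on a relatedness judgement shared by the unblinded deliverer of the training, with no control arm or independent review as a check, so attribution can lower the count behind a low-risk conclusion. The conflict between the two descriptions of the causality item is a plain textual error affecting the same variable.

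The size cannot be stated as a bias. At 18 participants the step is 5.6 points per reclassified injured participant. Under an assumed 20% all-injury risk, attributing half of the injuries elsewhere raises the chance of counting none or one from 9.9% to 45.0%. At an assumed 10% risk it goes from 45.0% to 77.4%, and at 30% from 1.4% to 22.4%. All of these rest on assumed risks, shares and cut-off.

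A reader might infer that the injury count alone decides H1, or that the investigator can be expected to misattribute events. The documents support neither: perceived safety is a separate criterion, and nothing in the text points to misattribution. This is a cheap improvement to an exploratory single-arm study.

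**What to change.** - **Section 2.4.3:** have the study doctor assign causality, with the principal investigator supplying the facts of each event but not its classification. Reconcile the causality item with 2.2.1 so that both sections name the same relationship.
- **Section 2.3.2 (H1):** report the count and incidence of all new or worsened injuries in weeks 1 to 16 beside the IST-related count, and state whether the low-risk conclusion holds on both. Keep the IST-related count; do not replace it.

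**Cost:** changes of wording. The study doctor is already in the team and all AEs are already recorded, so no new staff or data are needed. The all-injury figure will be equal to or higher than the related one and will include background events that a single-arm design cannot separate out. The comparison with literature rates should therefore say which kind of count each source uses.
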